#### Analysis

For the primary outcomes of change in participant level of social need and episode completion, we will use mixed effects modeling, assuming missing at random, to determine if patients who receive community services navigation have greater reduction in social needs and if patients who receive the intervention complete their breast cancer screening episode of care and recommended follow up care. We will examine the interaction between time (conditional on baseline, 6, and 18 months) and intervention. We will analyze the time to follow-up completion using Cox proportional hazard modeling.

For the secondary outcome of community resource use, we will use a similar mixed-effects two-level model and utilize a log link function for a negative binomial regression for the count of social services used. We assume that the number of services will not be normally or dichotomously distributed. For the other secondary outcome of screening behavior, we will use the same mixed-effects two level model with log link function for a negative binomial regression.

Participant demographics will be compared between groups via t-Test and Fisher exact testing, Chi-squared testing, or Wilcoxon-Mann-Whitney test where appropriate.

To determine the sample size, power and sensitivity analyses were conducted with G-Power 3.1. We used a RMANOVA model with 3 total measures as a conservative approach for our mixed-effects model. We assume power = 0.95, alpha = 0.05, and two-tailed significance testing. Results indicate a small effect size (Cohen’s d = 0.09) can be detected. Therefore, recruitment of 1,450 patients with an attrition rate of 20%, will result in an analyzed sample of 1,160, which is sufficient power to detect a clinically meaningful effect. Unpublished pilot data obtained from participants who reported they had a social need the average amount of social needs was 3.06 with a standard deviation = 2.08. We will have 95% power to detect a reduction of social needs to 2.87.

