#### Outcomes

The primary outcomes for this study are (1) change in participants’ social needs, and (2) episode completion. Social needs are determined by the SINCERE assessment, which the participant takes at baseline, 1 month, 6 months, and 18 months [15]. Episode completion in regard to follow-up care will be determined by patient-reported surveys and by accessing the patient’s electronic health record (EHR) to determine if they attended their follow-up care appointment(s) (e.g. additional imaging, biopsy, meeting with a specialist, or starting breast cancer treatment). As in our prior work within the national PROSPR I consortium ([name], MPI) [20], we define a breast screening episode follow-up within a specified time interval based on Breast Imaging-Reporting and Data System (BI-RADS) category [21, 22]; specifically: BI-RADS 0,4,5 – episode completion within 3 months; BI-RADS 3 – episode completion within 9 months. The BI-RADS 3 classification is used infrequently (~ 2% of patients nationally, and < 1% at the University of Utah), and therefore, we anticipate we will capture > 99% of follow-up at our 6-month data collection point [21]. Data on both episode completion and time to completion will be collected.

The secondary outcomes are (1) social service utilization and (2) prevention and screening behaviors relating to breast, cervical, colorectal, and colon cancers. Health outcomes include trust in the healthcare system [25], cancer worry [26], and social support [27]. These will be assessed through patient reported outcomes at various timepoints throughout study enrollment.

Social service utilization data is gathered through patient reported measures as well as reports from 211 on participant utilization of social services. 211 records outcome at follow up, referral outcome, and if the patient’s situation has changed. Prevention and screening behaviors include next annual mammogram, cervical cancer screening, and colorectal cancer screening. We will ask women to self-report, and will also examine EHR records to capture guideline-concordant use of wellness visits.

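### The only contrast stated for the primary-outcome mixed model, time by intervention, does not suit episode completion, and the article does not say which analysis decides that outcome

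*Protocol article*

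**What the plan says.** The protocol article (Outcomes) names two primary outcomes: change in social needs and episode completion. Social needs are measured repeatedly with SINCERE. Episode completion is defined by a window that depends on the index mammogram: "BI-RADS 0,4,5 – episode completion within 3 months; BI-RADS 3 – episode completion within 9 months". BI-RADS 3 is put at under 1% of local patients, and on that basis the authors write that "we anticipate we will capture > 99% of follow-up at our 6-month data collection point". They add: "Data on both episode completion and time to completion will be collected".

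The Analysis section gives one method for both outcomes: "For the primary outcomes of change in participant level of social need and episode completion, we will use mixed effects modeling". The only contrast it states follows: "We will examine the interaction between time (conditional on baseline, 6, and 18 months) and intervention". That sentence names no outcome, so it is not limited to social needs. The next sentence reads: "We will analyze the time to follow-up completion using Cox proportional hazard modeling". Neither the mixed model nor the Cox model is identified as the analysis that decides the episode-completion outcome.

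**The concern.** The Aim 2 hypothesis is a comparison between arms: more women complete the episode with navigation than without. The natural test compares the two proportions completing within the window, using one value per woman.

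A time-by-intervention term asks something else, namely whether the difference between arms changes over the measurement times. For a score that exists at baseline and can rise or fall, that is the right question. For a status that cannot yet have been reached at baseline, cannot reverse once reached, and by the article's own estimate is almost entirely settled by 6 months, it is not.

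Two things are at stake. If the stated contrast is applied to completion, it may fail to fit, or it may return a null result when navigation works. And if an arm effect, an interaction and a Cox hazard ratio all remain available, the deciding test for a primary outcome can be chosen after the data are seen.

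**Working it through.** **Inputs from the article.** Two arms with equal allocation; 1,450 recruited; 20% attrition; 1,160 analysed; two-sided alpha 0.05; one completion status per woman in a 3- or 9-month window; model times baseline, 6 and 18 months. The article gives no completion rate for usual care, so every rate below is an assumption.

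**The plan's own figures.** 1,450 × 0.80 = 1,160, as stated. The stated effect size is (3.06 − 2.87)/2.08 = 0.091, which agrees with 0.09. Both the effect size and the 95% power claim concern the social-needs score. No figure is given for episode completion, so there is none to reproduce.

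**What the stated contrast does with completion.** Four codings were tried with 580 women per arm.

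1. *One record per woman.* With a single time, the columns for time and for time by arm duplicate those for the intercept and arm. The design matrix has rank 2 of 4, so the interaction cannot be estimated.
2. *Status 0 for everyone at baseline, then the same value at 6 and 18 months, logit link.* The baseline log-odds are unbounded and the fit separates. In a fixed-effects logistic fit the interaction has a standard error of about 34,000.
3. *6 and 18 months only, with in-window status.* The value is the same at both times, so the interaction is exactly 0 whatever navigation does. With assumed true rates of 70% v 78% it was detected in 0 of 2,000 simulated trials. A simple two-proportion test has 87.5% power.
4. *Linear model with baseline fixed at 0.* The baseline-to-6-month interaction is (p_active − 0) − (p_usual − 0) = p_active − p_usual, the difference in proportions. Simulated power at 70% v 78% is 88%. This coding does answer the question, because it reduces to the simple comparison.

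**If late completions were counted at 18 months.** Take 80% v 86% completing in the window.

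- *30% of the remainder finish later in both arms.* The 18-month rates are 0.80 + 0.20 × 0.30 = 86.0% and 0.86 + 0.14 × 0.30 = 90.2%. The odds ratio goes from 1.54 to 1.50, and with 725 per arm the 6-v-18-month interaction is significant in about 5% of simulated trials.
- *Late catch-up is 50% in usual care and 30% in the active arm.* The 18-month rates are 90.0% and 90.2%, the odds ratio falls to 1.02, and the interaction is significant in about 93%.

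The rejection rate therefore depends on the assumed late catch-up. In neither case does it measure whether navigation raised in-window completion.

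**Power of a direct comparison.** Power = Φ[(d − 1.96·se0)/se1], where d is the difference, se0 = √(2·p̄(1 − p̄)/n) and se1 = √([p0(1 − p0) + p1(1 − p1)]/n). With p0 = 0.80, p1 = 0.86, p̄ = 0.83 and d = 0.06:

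- n = 725 per arm: se0 = 0.01973, se1 = 0.01967; Φ(1.085) = 86%.
- n = 580 per arm: se0 = 0.02206, se1 = 0.02199; Φ(0.763) = 78%.

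Detectable increase with 580 per arm:

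| Assumed usual-care rate | 80% power | 95% power |
|---|---|---|
| 50% | 8.2 points | 10.5 points |
| 70% | 7.3 points | 9.2 points |
| 80% | 6.2 points | 7.8 points |
| 90% | 4.5 points | 5.5 points |

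**The case against.** A reader might infer that the plan cannot answer Aim 2 at all. The document does not support that. The Cox model compares the arms on completion and bears directly on Aim 2, and Aim 2 also covers preventive care, which has its own model. It is equally too strong to say that the 3- and 9-month windows never enter the analysis: they define the outcome that is analysed.

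The interaction sentence can also be read more kindly. It names no outcome, its times include baseline, and the sentence before it gives the model's purpose for completion in terms that fit an arm effect. On that reading the interaction belongs to SINCERE, and completion is tested by arm, perhaps with clinic as a second level. Link function and coding are details that a condensed article may leave to a full protocol or SAP, and a linear coding with baseline at 0 recovers the arm difference. Nor is a near-chance rejection rate for the interaction a general result, since it rests on equal late catch-up in both arms.

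These points stand and they limit the finding. They do not remove it. The kind reading is not what the text fixes: completion is named in the mixed-model sentence and the only contrast given is time by intervention. The coding that works does so because it collapses to the simple comparison. The Cox model concerns time to completion, which the Outcomes section lists separately from completion itself. As stated, a woman who finishes after her window is still an event, unless follow-up is censored when the window closes.

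**Conclusion.** The point holds in a limited form. The stated time-by-intervention contrast does not suit episode completion: depending on coding, it is not estimable, separates, is identically zero, depends on late completions outside the window, or reduces to the between-arm comparison that could have been named directly. The article plans a relevant Cox analysis but does not say which analysis decides the second primary outcome, and it fixes no between-arm test of completion within the window.

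The structural part rests only on the article's own definition of the outcome and its expectation of more than 99% capture by 6 months. The power figures do not share that footing. The 86% (1,450 women) and 78% (1,160 women) are illustrations at an assumed 80% v 86%. They show what a direct test might achieve, not a shortfall in the plan.

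**What to change.** Three changes to the Analysis text:

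1. State that the longitudinal time-by-intervention mixed model applies to the SINCERE score only.
2. Name one primary Aim 2 test: a between-arm comparison of completion within the woman's BI-RADS window, with one value per woman, in all randomised women, by logistic regression or risk difference, adjusted for index BI-RADS category and with no time term.
3. State that the Cox model on time to completion is supportive.

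The cost is analysis wording only. Completion status and time to completion are already to be collected, so no new data or visits are needed. The wording should be settled before outcome data are examined. Once the team has a usual-care completion rate, it can state the detectable difference for this outcome alongside the one for social needs.

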### Hypotheses and aims

Central hypothesis: Community services navigation combined with social needs referrals will increase use of social services and improve breast cancer screening follow-up compared to the passive process of social service referrals alone.

Aim 1: Test whether the use of a community services navigation intervention in conjunction with social service referrals decreases social needs compared to the referrals alone (usual care).

Aim 1 Hypothesis: Patients who receive community services navigation will have fewer social needs over time when compared to patients who receive standard of care process of social service referrals alone.

Aim 2: Determine the impact of the community services navigation intervention (211 services) on breast cancer screening episode completion and preventive care utilization among women with self-reported social needs.

Aim 2 Hypothesis: Patients who receive the community services navigation intervention will complete their breast screening episode of care, e.g. additional imaging, follow-up visits, or biopsy and recommended follow-up and preventative services more than women who do not.

Aim 3: Qualitatively examine multilevel facilitators and barriers to successful engagement with community services and episode completion among underserved women with an abnormal breast cancer screen and self-reported social needs and explore the role of community service navigation.

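### The only term named for the social-needs outcome is a time-by-intervention interaction: on its likelier reading a valid but inefficient test of Aim 1 that gives no single effect estimate

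*Protocol article*

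**What the plan says.** The Aim 1 hypothesis, under Hypotheses and aims, is "Patients who receive community services navigation will have fewer social needs over time" than patients given referrals alone. The Analysis section proposes mixed-effects modelling under missing at random, "to determine if patients who receive community services navigation have greater reduction in social needs". It then gives the one term to be looked at: "We will examine the interaction between time (conditional on baseline, 6, and 18 months) and intervention". It names no arm difference at a visit and no difference averaged over visits. It does not say whether baseline is a covariate or a response, or whether baseline means are held equal across arms.

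The sample-size paragraph of the same section says: "We used a RMANOVA model with 3 total measures as a conservative approach for our mixed-effects model". Under Outcomes, the instrument (SINCERE) is one "which the participant takes at baseline, 1 month, 6 months, and 18 months". It is also the eligibility screen, so every participant completes it before randomisation.

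**The concern.** Aim 1 asks whether navigated women end up with fewer needs. In a randomised trial with a pre-randomisation measurement, the direct answer is one baseline-adjusted difference between arms. The stated term is something else, and its meaning depends on how the parenthesis is read.

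- **Baseline as one of three levels of time.** The interaction is a joint test that the change from baseline to 6 months and the change from baseline to 18 months are the same in both arms. It has two degrees of freedom and does not reduce to one estimate. If baseline means are left free, each change carries the noise of the baseline difference between arms.
- **Baseline as a covariate, with time meaning 6 and 18 months.** The interaction then asks only whether the effect differs between those two visits. A benefit that is present at 6 months and fully kept gives an interaction of zero.

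At stake are power that the existing data could supply and a single interpretable result for a primary outcome.

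**Working it through.** **Inputs from the article (Analysis; Intervention).** 1,450 enrolled, 20% attrition, 1,160 analysed, equal allocation, so n = 580 per arm; SD 2.08; mean 3.06 falling to 2.87; two-sided alpha 0.05; power 0.95. **Assumed.** Within-person correlation ρ, not stated: 0.3, 0.5 and 0.7 tried, with equal correlation between all visits. Also a normal approximation and complete data at the three visits.

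**The plan's own figure.** 1,450 × 0.8 = 1,160. (3.06 − 2.87)/2.08 = 0.19/2.08 = 0.091, which matches the stated d of 0.09. For the repeated-measures interaction, λ = N f² m/(1 − ρ). With N = 1,160, m = 3, ρ = 0.5 and f = 0.0471, λ = 15.44 and power is 95%; 2f = 0.094. So d = 0.09 can be reproduced as an interaction at ρ of about 0.5. A between-arm test at ρ = 0.5 gives a detectable f of 0.0865, which also rounds to 0.09. The figure therefore does not settle which test was sized.

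**Formulas for an effect of δ SD at both 6 and 18 months**

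- 2-df interaction, free baseline: λ = nδ²/[3(1 − ρ)]
- 2-df test, baseline adjusted or constrained: λ = nδ²/[(1 − ρ)(1 + 2ρ)]
- 1-df baseline-adjusted average: SE² = (2/n)[(1 + ρ)/2 − ρ²], z = δ/SE

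**Illustration at δ = 0.15** (0.15 × 2.08 = 0.31 needs), nδ² = 580 × 0.0225 = 13.05:

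| ρ | Free-baseline 2 df | Adjusted or constrained 2 df | Adjusted average, 1 df |
|---|---|---|---|
| 0.3 | λ = 13.05/2.1 = 6.21; 60% | λ = 13.05/1.12 = 11.65; 87% | z = 0.15/0.0439 = 3.41; 93% |
| 0.5 | λ = 13.05/1.5 = 8.70; 76% | λ = 13.05/1.0 = 13.05; 91% | z = 0.15/0.0415 = 3.61; 95% |
| 0.7 | λ = 13.05/0.9 = 14.50; 94% | λ = 13.05/0.72 = 18.1; 97% | z = 0.15/0.0352 = 4.26; 99% |

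At ρ = 0.5 most of the gain (76% to 91%) comes from the use of baseline, and the rest (91% to 95%) from one degree of freedom instead of two. For 95% power, the free-baseline test needs 1.8 times the sample of the adjusted average at ρ = 0.5 (2.2 times at 0.3, 1.5 times at 0.7). The smallest sustained difference detectable with 80% power at ρ = 0.5 is 0.33 needs against 0.24.

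**Covariate reading.** With the same effect at both visits, the 6-versus-18-month interaction is zero, and its power is alpha, 5%, at any effect size.

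**Effect present at 6 months and gone by 18 (δ = 0.15, ρ = 0.5).** The free-baseline interaction still has λ = 8.70 and 76% power. The constrained 2-df test has 81%. The averaged contrast sees 0.15/2 = 0.075, so z = 0.075/0.0415 = 1.81 and power is 44%. A contrast named at 6 months has SE² = (2/580)(1 − 0.25) = 0.00259, z = 0.15/0.0509 = 2.95 and power 84%. If the effect halves by 18 months, the averaged contrast has 77% against 62% for the free-baseline interaction.

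**At the plan's own 0.19, read as a sustained arm difference, ρ = 0.5 (range for ρ 0.3 to 0.7).** Free-baseline interaction 34% (26% to 54%); constrained 2-df test 49% (45% to 64%); adjusted average 59.5% (55% to 74%).

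**The case against.** The strongest defence is that the interaction is the standard test of a different change between arms. The parenthesis lists three visits, the model is meant to show a greater reduction, and the sample size uses three measures. A reduction can be an interaction only if baseline is a level of time. All of this stands. A reader might infer that the planned test is blind to a sustained benefit, but the documents do not support that as the likely meaning: with three levels of time, a sustained benefit is a non-zero interaction.

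A second objection is that the size of the loss is uncertain. The article fixes neither a 2-df omnibus test nor free baseline means, and gives no correlation. This also stands. If the mixed model already constrains baseline, the loss against the adjusted average at ρ = 0.5 is only about 4 points. With free means at ρ = 0.7 it is about 5 points; at ρ = 0.3 it is 33.

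Third, the averaged contrast is not better under every pattern. The 211 contact described under Intervention is a call within 48 hours and a follow-up at 2 weeks, so a fading effect is plausible. This stands against the average as an automatic choice. It does not count against baseline adjustment, which raised or at least kept power under every pattern tried.

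Finally, the interaction is to be examined and is not labelled the sole confirmatory test, and a journal article may leave model detail to a fuller document. That is fair as to the detail. The article did, however, choose to name a term for a primary outcome, and on either reading that term answers Aim 1 less well than a baseline-adjusted arm contrast.

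**Conclusion.** The point holds as one of efficiency and clarity. On the likelier reading the test is valid. Run with 2 df and free baseline means, it gives up 33, 20 and 5 percentage points of power at ρ of 0.3, 0.5 and 0.7 against a baseline-adjusted average for a sustained 0.15 SD effect (from unrounded values), and it gives no single estimate. Failure to detect a sustained effect is confined to the less likely covariate reading. The wording does not strictly exclude that reading, which is reason enough to settle it before data are seen.

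The figures rest on 580 per arm, equal correlation between visits, an assumed ρ and a constant effect at 6 and 18 months. The change would not make the sample-size statement true: for 3.06 against 2.87 as an arm difference, no test examined reaches 95% with ρ between 0.3 and 0.7. That is a separate problem.

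**What to change.** State how baseline enters the model: baseline SINCERE as a covariate, or baseline means constrained equal across arms. Name one baseline-adjusted arm contrast in the SINCERE count as the primary Aim 1 test, either at a named visit or averaged over stated post-baseline visits. Choose between these, with a reason, from the expected course of the effect, because the average loses to the interaction if the effect has gone by 18 months. Say whether the 1-month SINCERE is included, since it is collected but appears in neither the analysis parenthesis nor the count of three measures. Keep the time-by-intervention interaction as a secondary description of how the effect develops.

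This is a change of analysis wording only. It needs no added participants, visits or data, since every participant already has a baseline SINCERE.

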#### Intervention

After providing informed consent and authorization, all participants will be randomized using the REDCap randomization function, with equal allocation to two arms: the usual care group or the active referral group.

The usual care group is provided the contact information for 211 if they choose to use it, but 211 does not reach out to these participants. 211 will receive the information of all participants, including those in the usual care group. If a usual care group participant reaches out to 211, they will note this for study records.

211 will reach out to all patients randomized to the active referral group within 48 h of receiving their information via REDCap. The 211 team will discuss the reported social needs with participants and match them with appropriate community resources that can help address their social needs. The 211 teams will also follow up again at 2 weeks with participants to ask if the participant has connected with services and offer additional support connecting to the social service referrals as needed.

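### Screening behaviour is described as done/not-done items but is assigned a negative binomial model, whose standard errors are too wide by an amount that grows with uptake

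*Protocol article*

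**What the plan says.** The Outcomes section of the protocol article lists two secondary outcomes, social service utilization and prevention and screening behaviours. It describes the second as follows: "Prevention and screening behaviors include next annual mammogram, cervical cancer screening, and colorectal cancer screening". On the data sources it says: "We will ask women to self-report, and will also examine EHR records to capture guideline-concordant use of wellness visits". It defines no count, score or sum.

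The Analysis section first assigns a mixed-effects negative binomial regression with log link to the count of social services, with this reason: "We assume that the number of services will not be normally or dichotomously distributed". It then carries the model over to the "other secondary outcome of screening behavior, we will use the same mixed-effects two level model with log link function for a negative binomial regression". It gives no separate reason for screening and does not mention robust standard errors. It also states no uptake, effect size or power for this outcome: the power statement in that section concerns social needs.

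**The concern.** A woman either has her next yearly mammogram within follow-up or does not, and the same holds for the cervical and colorectal tests. The reason offered for the negative binomial is that the number of services is neither normal nor dichotomous. Screening items, on their natural reading, are the dichotomous case that this sentence sets apart.

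A negative binomial model takes the variance to be at least as large as the mean. A 0/1 item cannot meet that, and extra dispersion cannot repair it, because the dispersion parameter only adds variance. The fitted dispersion goes to its zero bound and a Poisson model is left, which still overstates the variance. Confidence intervals would then be too wide and p-values too large. A real benefit on preventive care utilization, which is a named part of Aim 2, could be reported as no difference.

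**Working it through.** **Inputs from the protocol article**
- Analysed sample (Analysis): "recruitment of 1,450 patients with an attrition rate of 20%, will result in an analyzed sample of 1,160". Check: 1,450 × (1 − 0.20) = 1,160.
- Allocation (Intervention): "with equal allocation to two arms: the usual care group or the active referral group". So 1,160 / 2 = 580 per arm.
- Test level (Analysis): 0.05, two-sided. It is stated for social needs and used here for lack of another.

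**Assumptions, because the article gives no figure**
- Control uptake p1 from 5% to 90%.
- Intervention uptake p2 set so that a correct binary test has 80% power.
- One 0/1 outcome per woman, model-based standard errors, no random effects.

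**Formulas for the log risk ratio, n = 580 per arm**
- Poisson-limit model SE = sqrt(1/(n·p1) + 1/(n·p2))
- True SE = sqrt((1−p1)/(n·p1) + (1−p2)/(n·p2))
- With no difference between arms, the ratio of the two is 1/sqrt(1−p).
- Power of the planned test = Φ((ln(p2/p1) − 1.96 × model SE) / true SE)

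**Worked line, p1 = 50%, p2 = 58.2%.** True SE 0.0544 and model SE 0.0801, so the ratio is 1.47. ln(0.582/0.500) = 0.152. Power = Φ((0.152 − 1.96 × 0.0801)/0.0544), which is about 46% with these rounded inputs and 47% unrounded.

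| p1 | p2 | True SE | Model SE | Ratio | Power, correct test | Power, planned test |
|---|---|---|---|---|---|---|
| 5% | 9.3% | 0.2225 | 0.2301 | 1.03 | 80% | 78% |
| 10% | 15.6% | 0.1577 | 0.1683 | 1.07 | 80% | 76% |
| 20% | 27.0% | 0.1075 | 0.1225 | 1.14 | 80% | 72% |
| 30% | 37.8% | 0.0828 | 0.1015 | 1.23 | 80% | 66% |
| 40% | 48.2% | 0.0666 | 0.0888 | 1.33 | 80% | 58% |
| 50% | 58.2% | 0.0544 | 0.0801 | 1.47 | 80% | 47% |
| 60% | 67.9% | 0.0443 | 0.0736 | 1.66 | 80% | 33% |
| 70% | 77.3% | 0.0353 | 0.0685 | 1.94 | 80% | 16% |
| 80% | 86.2% | 0.0266 | 0.0645 | 2.42 | 80% | 3% |
| 90% | 94.4% | 0.0171 | 0.0612 | 3.57 | 80% | 0% |

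**Actual level of the nominal 5% test**, from 2 × (1 − Φ(1.96/sqrt(1−p))): 4.4% at 5% uptake, 2.8% at 20%, 0.6% at 50% and 0.03% at 70%.

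**Simulation check** (400 trials per setting, Poisson limit, fixed effects only). Rejection with the model-based SE against a robust SE was 74% v 83% at 20% v 27% uptake, 47% v 79% at 50% v 58.2%, 15% v 81% at 70% v 77.3%, and 2% v 81% at 80% v 86.2%. A single negative binomial fit to 0/1 data with 60% uptake put the dispersion at about 0.00004, that is, at its bound, and returned no standard errors.

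**If the three items were summed to 0–3.** With common uptake p and pairwise correlation r, the mean is 3p and the variance is 3p(1−p)(1+2r), so variance/mean = (1−p)(1+2r).
- At r = 0 this is below 1 for every p. For p above 2/3 it is below 1 for every r.
- It can exceed 1: p = 0.2, r = 0.2 gives 0.8 × 1.4 = 1.12, and p = 0.3, r = 0.3 gives 0.7 × 1.6 = 1.12. At p = 0.5, r = 0.5 it equals 1.
- For 70% v 74% per item, power of the planned against a correct test is about 14% v 75% at r = 0, 20% v 55% at r = 0.3 and 22% v 46% at r = 0.5.

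**The case against.** **The size is not fixed by the documents.** A reader might infer that the standard errors are far too wide and that most of the power is lost. That depends on uptake, which the article never gives. Below about 30% uptake the SE is at most about 23% too wide. More than half of the 80% power is lost only above roughly 55% uptake. This objection stands, so the result is given as a range.

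**The planned model is not the one calculated.** The article specifies a two-level mixed model, with assessment at several time points. Within-woman correlation would change the SE ratio, in a direction that depends on whether the target is the overall arm effect or the time-by-arm interaction. This stands as a limit on the figures. It does not make a count distribution suitable for a 0/1 item.

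**The coding is not stated.** No sentence says that the variable is 0/1, and the wellness visits mentioned beside the screening tests could be counted. Robust standard errors would largely remove the problem, and a full analysis plan, not shown, may specify them. The point nevertheless concerns something stated: the article names a model, and the three behaviours that it lists do not read as counts.

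**Stronger readings that the documents do not support.** A reader might infer that any sum of the items is under-dispersed, but with positively correlated items at low to moderate uptake it need not be. A reader might also infer that women not due for a given test would be pooled with those who are. The article does not say so, and denominators for each test are ordinary analysis-plan content.

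**Conclusion.** The point holds in a limited form. The stated model does not match the outcome as described, and the only justification in the text belongs to the other secondary outcome. For 0/1 items the SE is inflated by about 1/sqrt(1−p), which is minor at low uptake and severe at high uptake: the planned test keeps 72% power at 20% uptake, 47% at 50% and 16% at 70%, where a correct test has 80%. These figures assume 580 women per arm, one outcome per woman, model-based standard errors and no random effects.

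For 0/1 items the error is conservative: it hides differences and does not create false positives. It affects a secondary outcome and leaves episode completion, the primary outcome under Aim 2, untouched. It is worth correcting before analysis but does not threaten the trial's main conclusions.

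**What to change.** In the Analysis section, replace the negative binomial for screening behaviour with a separate binary analysis of each test: a logistic mixed model, or a log-link model with robust variance if a risk ratio is wanted. In the simulation above, the log-link model with robust variance brought power back to about 79% to 83%. Keep the negative binomial for the count of social services only. In the Outcomes section, state that each screening behaviour is coded done or not done; if a count is really intended, define it and justify its distribution separately.

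The cost is analysis wording. Data collection and sample size do not change.
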